##### SDS

3.7.3.2

SDS has a total of 20 items, each item is marked by 1–4 points, the total score is multiplied by 1.25 and rounded to an integer to get the standard score. The standard score normal upper limit reference value is 53 points; 53–62 points for mild depression, 63–72 points for moderate depression, and 72 points or more for severe depression.

##### SAS

3.7.3.3

SAS has a total of 20 entries, each entry is marked by 1–4 points, the total score is multiplied by 1.25 and rounded to an integer to get the standard score. The boundary value of SAS standard score is 50 points; 50–59 points for mild anxiety, 60–69 points for moderate anxiety, and 69 points or more for severe anxiety.

##### FSS

3.7.3.4

FSS has a total of 9 items, each scored on a scale of 1–7, with higher scores being associated with greater fatigue.

Primary and secondary outcomes will be evaluated at the following time points: Group 1 (0, 4 weeks), Group 2 (0, 4, 6 weeks), Group 3 (0, 4, 6, 8 weeks), and at follow-up (the first and third month after the end of treatment). The study schedule is depicted in Table 2.

**Table 2 tab2:** Study schedule.

Study period	Observation	Baseline	Treatment phase	Follow-up	
Timepoint	<7 days	0 week	4, 6, or 8 weeks	1 month	3 months
Enrollment					
Eligibility	×				
Informed consent		×			
Allocation		×			
Interventions					
Group 1			×		
Group 2			×		
Group 3			×		
Outcomes					
ISI		×	×	×	×
PSQI		×	×	×	×
SDS		×	×	×	×
SAS		×	×	×	×
FSS		×	×	×	×
Use of sleep medications			×	×	×
ISI < 8 points			×	×	×
Adverse events			×		

PSQI, Pittsburgh Sleep Quality Index; ISI, Insomnia Severity Index; SDS, Self-Rating Depression Scale; SAS, Self-Rating Anxiety Scale; FSS, Fatigue Severity Scale.

#### Other outcomes

3.7.4

The percentage of participants with ISI < 8 points will be considered in our outcomes. During the observation period, in order to clarify whether acupuncture can reduce the use of sleep medication, we will record the type, dose, frequency, and duration of the participant’s daily sleep medication.

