## Objectives

2

To compare the dose-effect relationship of different acupuncture courses on CID.

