### Randomization and blinding

3.4

Dynamic block randomization will be used to assign participants to three groups at a 1:1:1 ratio. The online central randomization system is undertaken by Chengdu CIMS Medical Technology Co. The generation of the randomized sequences will be completed by the designated investigator and participants will be given a unique number assigned by the system. Electronic data collection and data management systems will be set up by independent personnel.

The physicians responsible for the acupuncture treatments and participants in this study cannot be blinded. The data collectors, statistical analysts, and efficacy evaluators are unaware of the groupings.

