### Intervention

3.6

Participants in the three groups receive the same acupuncture treatments three sessions a week with at least 1 day between the two treatments: Group A (12 sessions for 4 weeks), Group B (18 sessions for 6 weeks), and Group C (24 sessions for 8 weeks). The acupoints will be selected as Baihui (GV20), Yintang (GV29), Anmian (EX-HN22, bilaterally), Shenmen (HT7, bilaterally), Neiguan (PC6, bilaterally), and Sanyinjiao (SP6, bilaterally). The localization of the acupoints refers to the national standards of the People’s Republic of China issued by the State Bureau of Technical Supervision, “Nomenclature and location of acupuncture points” (GB/T12346-2006) and “Nomenclature and location of extra points in common use” (GB/T 40997–2021). The localization of the acupuncture points is shown in Figure 2.

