6. Control or comparator interventions	(6a) Rationale for the control or comparator in the context of the research question, with sources that justify this choice	The acupuncture regimen is the same for each group and based on traditional acupuncture theory, literature search and expert’s consensus.	(6b) Precise description of the control or comparator. If sham acupuncture or any other type of acupuncture-like control is used, provide details as for Items 1–3 above.	All three groups will receive the same real acupuncture treatment

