### Statistical analysis

3.10

All statistical analysis will follow the intention-to-treat (ITT) principle, and the missing values will be supplemented by last observation carried forward (LOCF). For variables with normal distribution, one-way analysis of variance (ANOVA) will be used for comparison inter-group comparison, and paired samples *t*-test will be used for intra-group comparison. Kruskal-Wallis test will be used for non-normal distributed variables. Repeated measurements at different time points will be analyzed by using repeated-measures ANOVA. Data values will be mainly presented as the mean ± standard deviation or the median ± quartile spacing. While Chi-Square test/Fisher’s Exact test will be adopted to analyze categorical data. Categorical variables will be expressed as numbers and percentages. All statistical tests being bilateral at *p* < 0.05. Data analysis will be performed using IBM SPSS version 26.0 software (IBM Corp, New York).

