### Advantages and limitations

4.1

This is a head-to-head comparative effectiveness trial. To our knowledge, this study is the first to directly observe the dose-effect relationship of acupuncture for CID using different acupuncture courses as a starting point. Second, we are not restricting participants from using sleep medications. During the study period, we will follow participants’ use of psychotropic medications (e.g., antidepressants, anxiolytics) and/or sleep medications. In addition, in order to minimize the bias caused by the details of acupuncture, we unified the acupuncture protocol, including the number of needle insertions, depth of insertion, needle type, response sought, needle frequency, and retention time.

However, there are some limitations of the study. First, the uniformity of the acupuncture protocol also meant that the points are not to be dialectically selected and individual differences will not be considered, which may underestimate the overall efficacy of acupuncture. Second, due to the specificity of the study design and acupuncture, we are unable to blind patients and acupuncturists. The researchers responsible for data collection, statistical analysis, and efficacy evaluation are unaware of the groupings to minimize bias in reporting subjective results. In addition, the results of this study are subjective, and we do not use aids for the objective assessment of sleep, such as polysomnography and the Mean Sleep Latency Test (MSLT), which are not applicable to the routine assessment of CID with poor patient compliance (11).

The scope of the dose-effect relationship of acupuncture is very wide. In this trial, one of the factors that may have a strong influence on the efficacy (different treatment courses) will be selected for comparative study. In future studies, under the premise of relative quantification of manipulation, different number of sessions per week, continuous treatment or interval treatment, the choice of unilateral or bilateral acupoints, and needle retention time will all be the focus of research on the dose-effect relationship of acupuncture for CID. At the same time, we prefer to assess clinical efficacy by a combination of subjective and objective indicators if we can obtain consent from a large number of participants.

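### Section 3.7.4 asks whether acupuncture can reduce sleep-medication use, but with acupuncture in every arm the trial can only answer whether a longer course lowers use compared with a shorter one

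*Protocol article*

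**What the plan says.** Section 3.7.4 (Other outcomes) gives one purpose for recording the type, dose, frequency and duration of daily sleep medication: "in order to clarify whether acupuncture can reduce the use of sleep medication". The abstract lists medication use among the secondary outcomes.

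The design is described elsewhere as follows.

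- Objectives (Section 2): "To compare the dose-effect relationship of different acupuncture courses on CID".
- Table 1, item 6b: "All three groups will receive the same real acupuncture treatment".
- Intervention (Section 3.6): the groups have 12 sessions over 4 weeks, 18 over 6 weeks and 24 over 8 weeks, at the same points and weekly frequency.
- Randomization (Section 3.4): the system will "assign participants to three groups at a 1:1:1 ratio". Participants and acupuncturists are not blinded.
- Statistical analysis (Section 3.10): between-group tests are planned, and for normally distributed variables "paired samples *t*-test will be used for intra-group comparison". No analysis is named for medication use.
- Table 2: sleep-medication use is marked in the treatment phase and at both follow-up visits, but not at baseline.
- Advantages and limitations (Section 4.1): "we are not restricting participants from using sleep medications". The limitations do not mention that there is no comparator without acupuncture.

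**The concern.** The aim in Section 3.7.4 and the randomised comparison are different questions. The first concerns acupuncture as such. The second concerns 4, 6 or 8 weeks of the same acupuncture. A between-group test therefore does not address the aim as written, and the only analysis in Section 3.10 that appears to address it is change within a group.

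Such change is uncontrolled. It mixes any effect of needling with several other things:

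- the natural course of insomnia;
- regression to the mean after entry at an ISI of 10 or more (Section 3.3);
- the lifestyle advice given alongside treatment (Table 1, items 4a and 4b);
- changes in medication that participants are free to make.

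What is at stake is the conclusion that can be drawn on a secondary outcome. If the aim stands as worded, the final report is invited to answer a question for which the trial has no comparator.

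**Working it through.** The protocol gives no figure for the medication outcome, so there is none to reproduce. The check compares what each planned contrast estimates with what Section 3.7.4 asks.

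**1. What each contrast estimates.** Let b(w) be the change in medication use by week w from randomisation that would occur without acupuncture. Let e4, e6 and e8 be the effects of the three courses by that week.

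- Change within Group A = b(w) + e4. Change within Group C = b(w) + e8. With no arm in which e = 0, b(w) cannot be estimated, so neither e4 nor e8 can be separated from it.
- Group C minus Group A at the same w = e8 − e4. The term b(w) cancels because allocation is randomised.
- If that difference is zero, then e8 = e4. This is equally true if both courses do nothing and if both work equally well.

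The randomised contrast thus answers the course-length question, and a null result leaves the question in Section 3.7.4 open.

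**2. Timing.** The background term cancels only if w is the same in both arms. Section 3.7.3.4 puts later visits "at follow-up (the first and third month after the end of treatment"), so they are anchored to the end of treatment. Taking a month as about 4 weeks, the visits fall at these weeks from randomisation:

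| Visit | Group A | Group B | Group C |
|---|---|---|---|
| End of treatment | 4 | 6 | 8 |
| First month | about 8 | about 10 | about 12 |

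Comparing like-named visits for A and C leaves a gap of 8 − 4 = 4 weeks, so b(4) is set against b(8) and does not cancel. Group A's first-month visit and Group C's end of treatment both fall at about week 8. By then Group C has had 24 − 12 = 12 further sessions and Group A none, so this is a randomised comparison at a common time. Group B has no visit at week 8 (its visits are at weeks 4, 6 and about 10), but Section 3.7.4 describes a record of daily medication, from which the same weeks could be taken.

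**3. Baseline.** Table 2 has no baseline mark for sleep medication. The PSQI is marked at baseline and contains a sleep-medication component scored 0 to 3, so some baseline information exists, but not the type, dose and frequency that Section 3.7.4 wants. As scheduled, change from baseline in the recorded measure is not clearly available.

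**4. How informative the course-length comparison could be.** The sample size was set on the ISI. The protocol's formula, with SD 3.8 and means 10.5, 9.5 and 8.0, gives 2.52² × 3.8² / 1.5833 = 57.9, which agrees with its 58 per group. Take 58 evaluable in each of Groups A and C, a two-sided 5% test of two proportions and 80% power. The protocol gives no medication-use rate, so the Group A rate is assumed over a range:

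| Assumed users in Group A | Users in Group C needed for 80% power |
|---|---|
| 20% | 3.4% |
| 30% | 9.5% |
| 40% | 16.8% |
| 50% | 25.1% |

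Only a large difference would be detected reliably, which is a further reason not to read much into a null result.

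**The case against.** The strongest reply is that this is one subordinate clause. The objective is stated correctly as a comparison of courses, the abstract names the outcome neutrally, and nothing in the sample size or the primary analysis depends on the clause. This stands, and it limits the severity. It does not remove the point, because the clause is the only purpose given for collecting the outcome.

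A second reply is that a randomised gradient would itself be evidence. This also stands in part. A reader might infer from the missing control that nothing in the trial can bear on acupuncture and medication use, and that goes too far. Lower use in Group C than in Group A at week 8 would be randomised, though unblinded, evidence that further sessions reduce use. It would still not measure the effect of acupuncture against none.

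A third reply is that the protocol never says a fall over time will be put down to acupuncture. That is correct. A reader might infer it from the stated purpose together with the paired tests, but those tests are a general provision, no analysis is assigned to medication use, and Table 2 schedules no baseline for it. The fault is an aim that the design cannot meet, not a false conclusion already drawn.

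Finally, a separate analysis plan may specify the analysis. It cannot supply a comparator that the design lacks.

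**Conclusion.** The point holds in this form: the aim in Section 3.7.4 cannot be answered as worded, because no comparison of acupuncture with no acupuncture exists and within-group tests give only uncontrolled change. The trial can answer the narrower question of whether a longer course lowers medication use compared with a shorter one, provided the arms are compared at the same time from randomisation. A null result on that question would not speak to acupuncture as such.

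No bias can be sized from the document, which gives neither a rate of medication use nor a rate of spontaneous reduction. Any assumed spontaneous reduction would simply reappear as the apparent within-arm effect. The conclusion rests on the arms as described in Section 3.6 and Table 1, and the week-8 alignment takes one month as about four weeks. The outcome is secondary and the primary ISI comparison is unaffected, so the severity is minor.

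**What to change.** 1. In Section 3.7.4, restate the aim as whether a longer course of acupuncture lowers sleep-medication use compared with a shorter course.
2. Analyse medication use between arms over the same calendar window from randomisation, not at visits anchored to the end of treatment. The weeks up to week 8 are one example. For Group B, which has no visit then, take those weeks from the daily record.
3. Mark sleep-medication use at baseline in Table 2, so that the between-arm comparison can be adjusted for it.
4. State that within-arm changes are descriptive and support no conclusion that acupuncture itself reduces use. Add the absence of a comparator without acupuncture to the limitations in Section 4.1.

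The cost is a narrower claim, one more baseline entry and slightly more analysis. Treatment, medication rules and sample size do not change. The baseline mark alone would not cure the problem: without the restated aim it would only make the uncontrolled before-after comparison easier to run.

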### Safety assessments

3.8

We will record the possible adverse events in detail during the treatment period, including the time of occurrence, duration, and treatment measures of the adverse events. Common adverse events of acupuncture may include pain, bruising, and localized swelling at the site of acupuncture, and these possible conditions will disappear on their own after pressure or rest. Serious adverse events will be reported to the Ethics Committee of the Hospital of Chengdu, University of Traditional Chinese Medicine in a timely manner.

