**Methods and design:**

This is a prospective, parallel, single center randomized controlled trial. Two hundred and one participants with CID will be randomly divided into three groups (Group A, Group B, and Group C). The three groups will be given acupuncture therapy for 4, 6, and 8 weeks, three sessions per week, with at least 1 day between sessions. Follow-up will continue until the third month after the end of treatment. The primary outcome is the Insomnia Severity Index (ISI), and secondary outcomes include percentage of ISI < 8 points, the Pittsburgh Sleep Quality Index (PSQI), Self-Rating Anxiety Scale (SAS), Self-Rating Depression Scale (SDS), Fatigue Severity Scale (FSS), medication use, and safety.

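### Adverse events are collected only during treatment, so the arms are watched for 4, 6 and 8 weeks and nothing is collected at the follow-up visits

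*Protocol article*

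**What the plan says.** The abstract of the protocol article includes safety in its list of secondary outcomes: "Fatigue Severity Scale (FSS), medication use, and safety".

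Section 3.8 sets the recording window: "We will record the possible adverse events in detail during the treatment period". It also fixes what is noted for each event: "including the time of occurrence, duration, and treatment measures of the adverse events". A further sentence sends serious adverse events to the ethics committee and gives no time limit.

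Section 3.6 makes the treatment period differ by arm: "Group A (12 sessions for 4 weeks), Group B (18 sessions for 6 weeks), and Group C (24 sessions for 8 weeks".

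Table 2 agrees with section 3.8. The row "Adverse events" has one mark, in the treatment column. ISI, PSQI, SDS, SAS, FSS, sleep medication and ISI below 8 are all marked in both follow-up columns. The text above the table places outcome assessments "at follow-up (the first and third month after the end of treatment".

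Section 3.10 has no sentence on adverse events. Its general rule summarises categorical variables as counts and percentages and tests them as follows: "While Chi-Square test/Fisher’s Exact test will be adopted to analyze categorical data".

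**The concern.** The randomised factor is course length, and course length also sets how long each patient is watched for harm. Group C is observed twice as long as Group A. An event unrelated to needling in week 6 is recorded in Group C but not in Group A, whose patients finished treatment two weeks before. If the result is summarised as the percentage of patients with any event, the longer course can look less safe with no difference in the underlying rate.

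A second loss occurs at data collection. No arm has adverse events collected in the three months after treatment, although every patient is seen twice in that time. An analysis plan can choose a better summary, but it cannot restore events that nobody asked about.

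The trial aims to identify the best course length and to support health economic evaluation, so harm by course length belongs to the comparison. The primary ISI comparison is not affected.

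**Working it through.** The plan contains no adverse-event rate or safety calculation to reproduce. The check covers observation time and then what a crude percentage would show.

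**Inputs from the protocol article**
- Treatment of 4, 6 and 8 weeks, with 12, 18 and 24 sessions (section 3.6).
- 67 patients per arm (section 3.5).
- Follow-up to 3 months after treatment, taken here as about 13 weeks.
- Two-sided 5% tests (section 3.10).

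**Step 1: observation time, assuming full adherence**
- Person-weeks with recording: 67 × 4 = 268, 67 × 6 = 402 and 67 × 8 = 536, a ratio of 1 : 1.5 : 2.
- Sessions: 67 × 12 = 804, 67 × 18 = 1206 and 67 × 24 = 1608, the same ratio.
- Person-weeks without recording: 67 × 13 = 871 per arm, 2613 in total. Recorded time is 268 + 402 + 536 = 1206. So 1206 / (1206 + 2613) = 1206 / 3819, or about 32% of trial time, has adverse-event recording.
- The unrecorded time includes weeks 5–8 in Group A and weeks 7–8 in Group B, when Group C is still being recorded.

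**Step 2: background events at an equal weekly rate**

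Let r be a weekly rate of events unrelated to needling, the same in every arm. The share of patients with at least one recorded event after w weeks is 1 − exp(−r × w). At r = 0.05:
- A: 1 − exp(−0.20) = 18.1%
- B: 1 − exp(−0.30) = 25.9%
- C: 1 − exp(−0.40) = 33.0%

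The expected number of patients affected is 67 × 0.181 = 12.1, 67 × 0.259 = 17.4 and 67 × 0.330 = 22.1.

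**Step 3: how often an unadjusted test would be significant**

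This is the simulated rejection rate of a 3 × 2 chi-square test with 67 per arm. The rates are assumptions.

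| Assumed weekly rate, equal in all arms | Share with an event in A, B, C | Significant |
|---|---|---|
| 0.5% | 2.0%, 3.0%, 3.9% | about 6% |
| 1% | 3.9%, 5.8%, 7.7% | about 11% |
| 2% | 7.7%, 11.3%, 14.8% | about 19% |
| 2.5% | 9.5%, 13.9%, 18.1% | about 23% |
| 5% | 18.1%, 25.9%, 33.0% | about 40% |
| 10% | 33.0%, 45.1%, 55.1% | about 64% |

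With an equal share of 26% in each arm the same test rejects about 5% of the time, so the excess comes from the unequal windows. It is slight when events are rare and large when they are common.

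**Step 4: needling events, for contrast**

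At an assumed 2% risk per session, 1 − 0.98^12 = 21.5%, 1 − 0.98^18 = 30.5% and 1 − 0.98^24 = 38.4%. This gradient is a real consequence of more sessions, so it is not counted as bias.

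**Step 5: what a rate does**

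At 5% per week the expected numbers of events are 13.4, 20.1 and 26.8. Divided by 268, 402 and 536 person-weeks, each gives 0.05. A rate removes the artefact for events that were recorded. It does nothing for those that were not.

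**The case against.** The strongest reply is that the unequal window is mostly the treatment contrast. The only events that section 3.8 names as expected are needle-site pain, bruising and swelling. They arise at sessions, and their total over the course is what someone choosing between 12, 18 and 24 sessions needs to know. This stands for needling events. It does not cover events unrelated to needling, and the size of the problem depends on how fully such events are captured, which the documents do not say.

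The second reply is that the time of each event is recorded, so rates per session or per week can be derived from the planned data. This also stands, and it confines the distortion to a crude percentage. A comparison over weeks 0–4 is possible too, but all arms receive the same treatment in that period, so it says little about course length. Events after treatment stay lost.

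Two stronger readings are tempting. A reader might infer that a chi-square test on adverse events is planned. Section 3.10 gives only a general rule for categorical data and does not mention adverse events, and exposure-adjusted summaries may properly sit in an analysis plan that is not shown. A reader might also infer that serious events in follow-up will go unreported. The serious-event sentence has no time limit, so the documents support only the narrower statement that no collection is scheduled after treatment.

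**Conclusion.** The point holds in a limited form. Recording stops with treatment in both section 3.8 and Table 2. This gives observation in the ratio 1 : 1.5 : 2 and no scheduled collection over about 13 weeks of follow-up in any arm. The lost follow-up events are the firmer part, because they rest on stated rules and no later analysis can repair them.

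The distortion of between-arm percentages is conditional. It needs events unrelated to needling, a crude percentage as the summary, and a rate high enough to matter. Under those conditions the chance of a spurious significant result runs from about 6% at 0.5% per week to about 64% at 10% per week. No single figure in that range can be preferred, because the documents give no event rate. The calculation also assumes full adherence and complete capture of background events during treatment.

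This should be changed, because the remedy is cheap and the data cannot be recovered afterwards. It does not threaten the primary analysis.

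**What to change.** 1. In Table 2, mark adverse events in both follow-up columns.
2. In section 3.8, extend recording to the 3-month visit in all arms, and ask for the onset date of each event.
3. Report needling-related events per course and per session.
4. Report other events as rates per person-week of observation, shown separately for the treatment and follow-up periods, in place of a crude comparison of percentages.

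The cost is one question at two visits already scheduled, and some added tabulation. The limitation is ascertainment. Patients attend three times a week during treatment and only twice afterwards, so follow-up events rest on recall and will be caught less completely. Comparisons across the two periods should be read as descriptive.

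A single comparison over a common window would not solve this. The shortest total observation is about 4 + 13 = 17 weeks, in Group A. Week 17 is not a visit in Group B or C, whose last visits fall at about weeks 19 and 21. Over those 17 weeks Group A would have 4 weeks of close contact and Group C would have 8.
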